In order to provide clinicians a complementary and alternative therapy for patients with KOA, and to determine whether evidence-based traditional Chinese medicine massage is a safe and effective therapy, we design and conduct the trial. Compared to topical NSAIDs (e.g., Diclofenac Emugel), which is strongly recommended (level 1a), massage is conditionally (level 3) recommended by the OARSI guidelines [6]. In the trial, we hypothesized that the evidence-based traditional Chinese medicine massage group would be non-inferior to the External Diclofenac Diethylamine Emulgel group in the treatment for KOA. In order to enhance the reliability of evidence-based traditional Chinese medicine massage in the treatment of KOA, we take the External Diclofenac Diethylamine Emulgel as the control group to evaluate the efficacy and safety in the study. In the overall design of the experiment, this scheme has randomization, control, and multi-center clinical trial.

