## Methods and design

The main purpose of this study is to compare the safety and efficacy of evidence-based traditional Chinese medicine massage and External Diclofenac Diethylamine Emulgel in KOA patients. Three hundred participants will be recruited for the study. Clinical data measurements, X-rays, and MRI scans will be evaluated at baseline and the end of treatment (Fig. 1). The study has been approved by the ethical committees of Guang’anmen Hospital (NO:201-135-KY-1) and registered in the Chinese Clinical Trial Registry (http://www.chictr.org.cn/showproj.aspx?proj=24457). The registration number is ChiCTR1800014400. The protocol will be reported following Standard Protocol Items: Recommendations for Interventional Trials (SPIRIT) statement.

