### Sample size

According to the literature, the average effective rate of treating knee osteoarthritis only through massage is 95.6% and 79.8% by application of external diclofenac diethylamine emulsion latex [15]. According to the sample size calculation formula, the minimum sample size of each group is *n* = 85.49. Considering expulsion case and getting significant results, at the same time, in order to implement layered research in the experimental group, we planned the ratio of the cases in the experimental group and the control group is 2:1, and the number of included cases was 300. There were 200 cases in the experimental group, and 100 cases were in the control group.

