### Safety outcomes

(1) Vital signs: body temperature, resting heart rate, respiratory, and blood pressure after 10 min of rest (systolic blood pressure, diastolic blood pressure). (2) Laboratory examination: blood routine (RBC, WBC, platelet, hemoglobin), urine routines (urine red cell, LEU, urinary protein, glycated hemoglobin alc), stool routine+occult blood, and liver function (ALT, AST), and renal function (BUN, Cr, 12 lead routine electrocardiogram). (3) Manipulation-related adverse events, such as ecchymosis, subcutaneous hemorrhage, fracture, and dislocation. (4) Drug-related adverse events, such as gastrointestinal tract response. (5) Other adverse events.

The safety of each therapy was evaluated by comparing the changes in blood and urine routine, liver and kidney function, electrocardiography before and after the treatment, and the incidence of adverse events during the treatment.

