### Statistical analysis

All statistical analyses will be performed with the SPSS software (SPSS 20.0, SPSS Inc., Chicago, IL, USA) by statisticians who are independent of the research team and blinded to the group allocation. Data analysis will be based on the intention-to-treat (ITT) principles. All numerical data will be presented as the mean ± SD, and categorical variables will be described with percentages (%). All the statistical tests are bilateral inspection; *p* < 0.05 is considered statistically significant. Paired *t* test or the paired rank sum test is used for the comparison within the groups; the *χ*^2^ test or Fisher’s exact probability method is used for the count data, and the Wilcoxon rank sum test is used for the rank data between groups. CMH *χ*^2^ test is used for the primary outcome of WOMAC improve rate. It is necessary to adjust the baseline and centers of the changes in WOMAC score between the groups with the covariance method.

The secondary outcome includes CSKO score, X-ray data, and MRI data, which are all measurement data, and a group *t*-test or the Wilcoxon rank-sum test is used for comparison between the groups. The *χ*^2^ test or Fisher’s exact probability method is used for participants’ dropout and adverse events rate analysis.

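### Comparing safety is part of the main purpose, but the only between-arm method named for adverse-event rates is a test of equality with low power for uncommon harms, which cannot by itself support a finding of safe or no worse

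*Protocol article*

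**What the plan says.** The Introduction gives one reason for the trial as "to determine whether evidence-based traditional Chinese medicine massage is a safe and effective therapy". Methods and design opens: "The main purpose of this study is to compare the safety and efficacy of evidence-based traditional Chinese medicine massage and External Diclofenac Diethylamine Emulgel". Safety therefore stands beside efficacy in the stated purpose.

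Safety outcomes lists the harms to be counted, including "Manipulation-related adverse events, such as ecchymosis, subcutaneous hemorrhage, fracture, and dislocation". It evaluates safety by before-and-after changes in laboratory values and ECG and by adverse-event incidence.

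For adverse-event rates, Statistical analysis offers the chi-square test or Fisher's: "Fisher’s exact probability method is used for participants’ dropout and adverse events rate analysis". The general rules there are "All the statistical tests are bilateral inspection" and a p-value "< 0.05 is considered statistically significant". It also says that "categorical variables will be described with percentages". It does not say when Fisher replaces chi-square.

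On size, the Sample size section says "There were 200 cases in the experimental group, and 100 cases were in the control group". The calculation uses effective rates only. No adverse-event rate, margin or detectable excess is given.

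**The concern.** A two-sided test of equality can end in two ways. It can reject, which shows a difference. Or it can fail to reject, which leaves open everything from no difference to an excess too small, or too rarely observed, for the trial to detect. Neither outcome is a positive finding that massage is safe or no worse than the gel, yet that is one of the questions the trial sets out to answer. The stated aim and the one named between-arm method for adverse events do not match.

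The mismatch matters most for uncommon harms, where failure to reject is the likely result even if massage causes a real excess. The safety half of the main purpose would then have no usable statement of how large an excess the data exclude.

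**Working it through.** **Inputs.** From the article: 200 massage and 100 gel patients (Sample size); two-sided tests, 0.05, chi-square or Fisher (Statistical analysis). Assumed: the true adverse-event rates, because the article gives none, and full follow-up of all 300 patients.

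**The plan's own figure.** The article states a minimum of 85.49 per group from effective rates of 95.6% and 79.8%. With the unpooled two-proportion formula and the rounded constant 10.5 (two-sided 5%, and 90% power, which is an assumption because no power is stated):

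n = 10.5 × [0.956 × 0.044 + 0.798 × 0.202] / (0.956 − 0.798)² = 10.5 × 0.20326 / 0.024964 = 85.49.

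The figure reproduces, but it concerns efficacy. It says nothing about the ability to detect harm.

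**Step 1. How many massage events against none on gel reach p < 0.05?** For 8/200 vs 0/100, with the 8 events fixed:

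- Fisher: the probability that all 8 fall on massage is C(200,8)/C(300,8) = 0.0372. Adding the tables that are no more probable (2, 1 or 0 events on massage: 0.0160 + 0.0022 + 0.0001) gives p = 0.0555.
- Uncorrected chi-square: 300 × (8 × 100 − 0 × 192)² / (200 × 100 × 8 × 292) = 4.11, p = 0.043.

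| Massage /200 vs gel 0/100 | Fisher p | Chi-square p, uncorrected | Chi-square p, Yates |
|---|---|---|---|
| 7 | 0.100 | 0.058 | 0.137 |
| 8 | 0.056 | 0.043 | 0.100 |
| 9 | 0.032 | 0.031 | 0.073 |
| 10 | 0.034 | 0.023 | 0.053 |
| 11 | 0.018 | 0.017 | 0.039 |

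The largest count that stays non-significant is 8 by Fisher, 7 by uncorrected chi-square and 10 with the Yates correction. At 8 vs 0 the smallest expected count is 8 × 100/300 = 2.67, below 5, where Fisher is the conventional choice; the article does not fix that choice. One gel event raises the count further: 12/200 vs 1/100 gives Fisher p = 0.067.

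**Step 2. Power to detect an excess on massage.** Sum the binomial(200, p₁) × binomial(100, p₂) probabilities over all tables with two-sided p < 0.05 and a higher rate on massage.

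| Assumed true rates, massage vs gel | Fisher | Chi-square, uncorrected |
|---|---|---|
| 2% vs 0% | 2% | 5% |
| 3% vs 1% | 6% | 10% |
| 4% vs 0% | 41% | 55% |
| 5% vs 1% | 33% | 41% |
| 10% vs 5% | 27% | 29% |
| 20% vs 10% | 59% | 61% |

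As a check on one row: with no gel events, Fisher needs at least 9 massage events, and P(X ≥ 9) for X ~ binomial(200, 0.04) is 0.407.

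**Step 3. What an interval would say instead.** For 8/200 vs 0/100 the risk difference is +4.0 points. The Wilson limits are 2.04% to 7.69% for massage and 0% to 3.70% for gel, so the Newcombe 95% limits are:

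- lower: 4.0 − √[(4.0 − 2.04)² + 3.70²] = −0.2 points;
- upper: 4.0 + (7.69 − 4.0) = +7.7 points.

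The reader then sees that an excess of up to 7.7 points is not excluded, whichever side of 0.05 the p-value falls. If no fracture or dislocation occurs on massage, the exact one-sided 95% upper bound for 0/200 is 1 − 0.05^(1/200) = 1.5%.

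**The case against.** The strongest reply is that the article sets no rule for concluding safety. A reader might infer from the test and the 0.05 threshold that p ≥ 0.05 will be reported as equal safety, so that a harmful massage would pass as no different. The documents do not support that: nowhere is non-significance equated with equal safety. This part of the reply stands, and the point does not rest on such a rule.

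A reader might also take the test to be the whole safety evaluation. It is not. Arm percentages will be shown, and laboratory and ECG changes are compared. Informed consent and participant safety requires adverse events to be recorded and reported to the ethics committee, with experts investigating the cause. Comprehensive suspension criteria provides for suspension on a significant safety problem. A cluster of fractures on massage would not go unnoticed because Fisher gave p = 0.056. This stands too. These safeguards work on single cases or within arms, however, and none of them estimates the excess of one arm over the other.

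Third, 8 against 0 must not be read as a limit for both named tests; it holds for Fisher only.

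Finally, trials are ordinarily sized on efficacy, the article sets no power target for harms, and intervals are often left to a full protocol or SAP. That would answer a complaint that intervals are merely missing. It does not fully answer this point, because the article does choose a between-arm method for a stated main purpose, and that method cannot deliver the conclusion sought.

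**Conclusion.** The point holds as a mismatch between a stated aim and the named method. It is an inexpensive improvement, not an error that invalidates the trial.

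The test of equality cannot by itself support a statement that massage is safe or no worse. Its power against an excess on massage is low throughout the range examined: from 2% (2% vs 0%) to 59% (20% vs 10%) by Fisher, and from 5% to 61% by uncorrected chi-square. The conclusion is the same under either test, although at 8 vs 0 the two fall on opposite sides of 0.05.

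The power figures rest on assumed event rates and on all 300 patients being followed; dropout would change them. The p-values in Step 1 depend only on the planned arm sizes and the counts shown.

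**What to change.** In Statistical analysis, make estimation the basis of the between-arm safety conclusion:

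- For any adverse event, serious adverse events and manipulation-related adverse events, report the risk difference (massage minus gel) with a 95% Newcombe or exact confidence interval.
- For rare serious harms such as fracture and dislocation, report an exact upper confidence bound for the massage-arm rate.
- Word the safety conclusion by the upper confidence limit, that is, by the size of excess that the data exclude.
- Keep the chi-square or Fisher p-value as descriptive, and state that non-significance is not evidence of equal safety.

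The cost is a short addition to the analysis text and a few intervals from data already being collected, with no extra patients. The downside is a more cautious safety claim.

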### Ethics and dissemination

The protocol was designed following the principles of the Helsinki Declaration. Participants will be informed of the study protocol, possible risks, and other related matters before entering the study and sign the informed consent before randomization.

All original medical record test results (personal data, test documents) will be confidential within the law. The results of the trial will be shown in tables and figures only, and no individual will be identified. All data collected from this study can only be used for this research. All members of the research team have ethical principles of confidentiality.

The results will be published in peer-reviewed academic journals and disseminated through conferences.

## Discussion

Massage treatments through pressing, pinching, flexion-extension, stretching, plucking, rubbing, and other bone-setting manipulations are all recommended. According to traditional Chinese medicine (TCM), massage on the epidermis of the body can stimulate and adjust the distribution of meridians, qi, and blood. According to modern medicine, massage may improve systemic immune and inflammatory profiles in healthy individuals [24]. As a supplementary and alternative therapy, massage has been widely used in clinical practice and was widely recommended by Chinese orthopedic experts.

Although some studies shown effectiveness and safety for all patients with KOA treatment by traditional Chinese massage or Diclofenac solution, however, as far as we know, our study will be the first randomized controlled and multicenter clinical trial. In this study, evidence-based traditional Chinese medicine massage treatment VS External Diclofenac Diethylamine Emulgel will be conducted in participants with KOA to observe the correlation between clinical manifestations and changes in X-ray and MRI, so as to further understand and identify the effectiveness and safety of both treatment methods.

In order to avoid the bias of results and improve the reliability of clinical results, we try to keep the baseline consistency as much as possible. Participants will be screened strictly according to the inclusion and exclusion criteria. All the researchers will be trained to understand the design of the study. To achieve blindness in the course of the intervention, the sealed envelopes should be attached to massage and External Diclofenac Diethylamine Emulgel before the intervention. In order to maintain the consistency of massage techniques, all Chinese massage therapists involved in the study have achieved strict massage training. In the study, MRI images of the affected limb were taken for MRI score of cartilage defects in both groups. All participants will be carried out in the above five hospitals. This study also has several limitations. First of all, Chinese massage therapists and participants in the waiting list will not be blinded due to the nature of the intervention. Secondly, the long-term efficacy of massage therapy will not be observed due to the observation treatment period of the study is only 10 weeks.

## Trial status

The study protocol was approved by the Ethical Committee of Guang’anmen Hospital on 08 January 2018. The study is currently in the recruitment phase, and the first participant was included on 1 June 2018. We predict that recruitment will be completed by September 2021.

## Data Availability

The full protocol for the study will be available from the corresponding author. Datasets generated or analyzed during the current study will not be publicly available due to data privacy. Results from the trial will be published in peer-reviewed international journals, and positive, negative, and inconclusive results will be published.

## Abbreviations

KOA: Knee osteoarthritis
ACR: American College of Rheumatology
TCM: Traditional Chinese medicine
NSAIDs: Non-steroidal anti-inflammatory drugs
CRF: Case report form
WOMAC: Western Ontario and McMaster Universities Osteoarthritis Index
CSKO: Chinese scale for knee osteoarthritis
MRI: Magnetic resonance imaging
